### Study Participants: Recruitment, Eligibility, and Randomization

The CATCH program receives 450–600 referrals of homeless adults per year, from hospitals or community agencies, prior to or shortly after hospital discharge for a mental health condition. Study participants were recruited among successive new CATCH program participants. Referrals to the study were made by CATCH staff during program intake meetings. Program participants expressing an interest in receiving information about the study were contacted by research staff to confirm interest, eligibility, to obtain informed consent, and to conduct a baseline assessment.

Study participants meet both CATCH program and CATCH-FI study eligibility criteria. Program eligibility criteria include: (1) current homelessness (defined as having no fixed place to stay for at least the past seven nights with little likelihood of finding a place in the upcoming month) or precarious housing (defined as currently occupying a single room in a multi-tenant building or house with shared common areas including bathroom and kitchen or a hotel/motel as a primary residence, and having a history of one or more episodes of absolute homelessness in the past year); (2) service provider-determined unmet mental health needs; (3) service user-determined unmet support needs; and (4) age 18 years or older. Excluded from the program are individuals with recent aggressive behavior requiring a higher intensity of support, or individuals whose illness severity necessitates residential care. To be eligible for the current study, in addition to meeting program eligibility requirements, participants must have been new referrals to CATCH, recently admitted or readmitted to hospital services, and have had at least one contact with the CATCH team.

Participants were randomized following the baseline interview using block randomization (55), which randomizes the participant list into groups 1:1 using blocks of four and six. This approach has the advantage of maintaining balanced group sizes throughout the recruitment process. The nature of the intervention precluded blinding of participants and study staff.

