### Sample Size

Previous research by our group (48) estimated that for those receiving usual care, the mean number of health-care contacts with program providers per month is 4.6. It was hypothesized that the intervention group will have at least 25% more health-care contacts with program providers per month (mean = 5.8) during the critical transition period. Because the primary outcome represents a count variable, sample sizes for Poisson regression were calculated using the formula provided in Signorini (56). Sample sizes of 67 per group achieve 80% power to detect a rate ratio of 1.25 with a significance level of 0.05 using a two-sided test. However, we expect an attrition rate of 22.0% (44), thus the final sample size per group is inflated by 22%, resulting in a total of 172 study participants. A subsample of study participants (*n* = 22), service providers (*n* = 12), and other key informants (*n* = 6) was estimated a priori as adequate to achieve saturation of qualitative findings and triangulation of data sources.

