##### Primary Outcome Analysis

Since program duration is customized for each participant, and may last between 1 and 6 months, we will calculate participants' person-months of program participation. This will allow us to estimate the rate ratio comparing the intervention and usual care groups with respect to the number of contacts with CATCH service providers per month. Therefore, for each participant, the total number of months in the program before discharge and the total number of contacts over the number of months in the program will be calculated. A Poisson regression model (PROC GENMOD) with total contacts as the dependent variable, group (CATCH-FI vs. CATCH-UC) as the covariate and an offset equal to the log (number of months spent on the program) will estimate the rate ratio and 95% confidence intervals, and the mean number of contacts per person-months and 95% confidence intervals in each group.

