##### Secondary Outcome Analysis

For continuous outcomes (i.e., QoLi-20, CSI, SF-36, and EQ-5D VAS), we will define change from baseline to 6-month follow-up as scores at 6 months minus scores at baseline. We will conduct analyses of covariance (ANCOVA) to compare changes from baseline between CATCH-FI and CATCH-UC, adjusting for baseline scores as a covariate.

For count outcomes (i.e., GAIN-SS, number of hospitalizations, number of days hospitalized, and number of emergency department visits) we will model the baseline and 6-month outcomes using generalized estimating equations (GEE) assuming the Poisson distribution or the negative binomial distribution, if over-dispersion is suggested by the data. The models will include the main effects of group (CATCH-FI vs. CATCH-UC) and time (6 months vs. baseline), and the interaction of group by time. A significant interaction will indicate that change from baseline is different between the groups. Rate ratios and 95% confidence intervals will be estimated.

The analysis of administrative data is similar to that of count outcomes, except that the period of consideration will be 12 months instead of 6 months pre and post-randomization.

For analyzing the number of days stably housed in the past 6 months, we will consider GEE with a Poisson or negative binomial distribution. The model will include the main effects of group and time, an interaction between group and time, selected covariates, and an offset represented by the natural log of residence days accounted during the 6 months interval. Rate ratios and 95% confidence intervals will be estimated to compare the rate of days stably housed per person-months.

For the WAI-SR, evaluated at the 6-month follow-up only, total scale, and sub-scales scores will be calculated and compared between the groups using the two-sample *t*-test or the Wilcoxon rank-sum test if extreme outliers are present. The correlation between WAI-SR and other outcomes at 6 months will be explored by estimating the Pearson or Spearman correlation coefficients, overall and by group.

SAS 9.4 will be used for all analyses and all analyses will use the intention-to-treat principle. We will consider multiple imputation to handle missing data. All statistical tests will be two-sided and a *p*-value of 0.05 or less will indicate statistical significance. There are no plans for interim analyses.

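### The primary contact count is fixed as a Poisson model with no allowance for over-dispersion; with even modest variation between participants the confidence interval is too narrow and the type I error exceeds 5%

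*Protocol article*

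**What the plan says.** Under Primary Outcome Analysis, the protocol article names the procedure, distribution, dependent variable and only covariate: "A Poisson regression model (PROC GENMOD) with total contacts as the dependent variable, group (CATCH-FI vs. CATCH-UC) as the covariate". The offset is the log of months in the programme, which the same section says may range from 1 to 6. This model supplies the rate ratio, its 95% confidence interval and the mean rate in each arm. Nothing is said about dispersion.

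Under Secondary Outcome Analysis, the count outcomes are modelled by GEE "assuming the Poisson distribution or the negative binomial distribution, if over-dispersion is suggested by the data". Days stably housed likewise has a choice of Poisson or negative binomial.

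The Sample Size section uses a Poisson calculation with a usual-care rate given as "the mean number of health-care contacts with program providers per month is 4.6" and states that "Sample sizes of 67 per group achieve 80% power to detect a rate ratio of 1.25". The test there is two-sided at the 5% level. The section gives no variance or dispersion for the contact count.

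**The concern.** A Poisson model with group as the only covariate sets the variance of each count equal to its mean, given time in the programme. That holds if all participants in an arm have the same underlying contact rate and their contacts arrive independently. The article suggests that rates differ. Under Study Design, contacts follow each participant's needs and preferences and may be in person or by phone, email or text. The Introduction describes poor engagement and high drop-out in this population. Under recruitment, the qualitative sample is chosen to span different levels of engagement.

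If rates differ between people, the model-based standard error is too small. The rate ratio itself remains a sensible estimate, but its interval overstates precision and the test rejects too often. A chance imbalance in how engaged the two groups happen to be could then be reported as an effect of the incentive. The safeguard is present for the secondary counts and absent for the outcome that decides the trial.

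**Working it through.** **Step 1: the plan's own figure.** Inputs from Sample Size: control rate 4.6 per month, rate ratio 1.25, two-sided 0.05, 80% power. Allocation is 1:1 (recruitment and randomization section). For a binary covariate split equally, with dispersion φ and T months per person, the Signorini formula is

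N = φ × (1.96 × √4 + 0.8416 × √(2 + 2/1.25))² / (T × 4.6 × (ln 1.25)²).

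With φ = 1 and T = 1, the numerator is (3.920 + 1.597)² = 30.4 and the denominator 4.6 × 0.0498 = 0.229. So N = 132.9, or 66.4 per group, rounded up to 67. Allowing for 22% attrition, 67/0.78 = 85.9, so 86 per group and 172 in total. Both stated figures reproduce, with no over-dispersion and one month of exposure.

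**Step 2: the effect of between-person variation.** Expected counts per person run from 4.6 × 1 = 4.6 to 4.6 × 6 = 27.6. Assume that, within a person, counts are Poisson, and that true rates vary between people with coefficient of variation CV. A count with mean μ then has variance μ + CV² × μ². For the log rate ratio, the true variance exceeds the Poisson variance by

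φ = 1 + CV² × E(μ²)/E(μ).

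Assume programme time uniform on 1 to 6 months (the article gives the limits, not the distribution). Then E(T) = 3.5, E(T²) = (6³ − 1³)/(3 × 5) = 14.33, and E(μ²)/E(μ) = 4.6 × 14.33/3.5 = 18.84. The true type I error of the planned test is 2 × [1 − Φ(1.96/√φ)], and the interval should be √φ times wider. The simulation column covers gamma-Poisson counts at 67 and 86 per arm.

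| Assumed CV | φ | √φ | Type I, formula | Type I, simulated |
|---|---|---|---|---|
| 0 | 1.00 | 1.00 | 5.0% | 5% |
| 0.1 | 1.19 | 1.09 | 7.2% | 7-8% |
| 0.2 | 1.75 | 1.32 | 13.9% | 14% |
| 0.3 | 2.70 | 1.64 | 23.3% | 23-24% |
| 0.5 | 5.71 | 2.39 | 41.2% | 40-42% |
| 0.7 | 10.23 | 3.20 | 54.0% | 54% |
| 1.0 | 19.84 | 4.45 | 66.0% | 66% |

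**Step 3: sensitivity to exposure.** With T the same for everyone, φ = 1 + 4.6 × T × CV². At CV 0.2, 0.3, 0.5 and 0.7, simulated type I error at 86 per arm is 7%, 10%, 18% and 27% if everyone contributes 1 month, and 18%, 30%, 49% and 60% if everyone contributes 6 months. Longer follow-up makes the problem worse, because each person contributes more contacts.

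**Step 4: does a corrected variance repair it?** On simulated data of the same kind, a sandwich variance gives about 5-6% and a Pearson scale about 5-7%. The Pearson scale is slightly high when exposure is unequal, because it estimates roughly 1 + 4.6 × 3.5 × CV² = 1 + 16.1 × CV² rather than 1 + 18.84 × CV².

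**Step 5: power with a valid test.** At rate ratio 1.25, 86 per arm and 1 to 6 months, power with a robust variance is about 96% at CV 0.3, 70% at CV 0.5 and 45-47% at CV 0.7.

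**The case against.** A reader might infer that the planned interval is certainly invalid and the type I error certainly far above 5%. The documents do not support that. They give no standard deviation or dispersion for the count. With no between-person variation the planned test is correct, and at CV 0.1 the excess is small. Any statement of size has to be conditional, and the range has to include its mild end.

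Contacts also follow a care plan, and 4.6 per month is about one a week. Regular scheduling could make counts within a person less variable than Poisson and offset part of the inflation. The calculation above does not model this, and the documents do not settle it. It is a reason for caution about the exact percentages. It does not justify assuming that variance equals mean.

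It can further be said that a condensed article may leave variance options to an analysis plan, and that the authors know of over-dispersion. That the standard errors will be unscaled is indeed an inference: the article names no scale or robust option, and a plain Poisson fit in PROC GENMOD holds dispersion at 1. But the primary model is spelled out down to procedure, covariate and offset, and the same Analyses section handles over-dispersion explicitly for other counts. The text as it stands fixes the primary model without it. This lowers certainty about what will be run, but does not remove the point.

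**Conclusion.** The point stands in conditional form. As written, the primary analysis has correct error rates only if contact rates barely differ between participants in an arm. Because each person is expected to contribute roughly 5 to 28 contacts, little heterogeneity is needed to matter: an assumed CV of 0.2 to 0.3 gives a type I error of about 14% to 24%, with an interval that should be 1.3 to 1.6 times as wide. These figures rest on the article's 4.6 contacts per month and its 1 to 6 month limits, and on assumptions of uniform programme time, gamma variation between people and Poisson variation within them. The absence of any dispersion provision for the primary outcome, beside an explicit one for the secondary counts, is a matter of text and needs no assumption.

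**What to change.** In Primary Outcome Analysis, prespecify a variance that allows for over-dispersion, with the same offset and not conditional on a dispersion test. Either of these will do:

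- Poisson regression with robust (sandwich) or Pearson-scaled standard errors. This is the smaller change, since it keeps the planned mean model and rate ratio. The sandwich version holds its level slightly better when programme time varies.
- Negative binomial regression with robust standard errors.

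Report plain Poisson standard errors at most as a sensitivity analysis.

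The change takes a line of wording and a procedure option, and no new data. Its real cost is a wider interval and lower power. The planned 80% is kept at CV 0.3 but not at CV 0.5 or 0.7 under the assumptions above. Recruitment is complete, so the sample size cannot be raised in response. The sample size calculation credits only one month of exposure per person, which gives some slack against moderate over-dispersion. The report should give the observed dispersion so that readers can judge the precision achieved.

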## Abstract

**Background:** People experiencing homelessness and mental illness have poorer service engagement and health-related outcomes compared to the general population. Financial incentives have been associated with increased service engagement, but evidence of effectiveness is limited. This protocol evaluates the acceptability and impact of financial incentives on service engagement among adults experiencing homelessness and mental illness in Toronto, Canada.

**Methods:** This study protocol uses a pragmatic field trial design and mixed methods (ClinicalTrials.gov Identifier: NCT03770221). Study participants were recruited from a brief multidisciplinary case management program for adults experiencing homelessness and mental illness following hospital discharge, and were randomly assigned to usual care or a financial incentives arm offering $20 for each week they attended meetings with a program provider. The primary outcome of effectiveness is service engagement, measured by the count of participant-provider health-care contacts over the 6-month period post-randomization. Secondary health, health service use, quality of life, and housing outcomes were measured at baseline and at 6-month follow-up. Quantitative data will be analyzed using descriptive statistics and inferential modeling including Poisson regression and generalized estimating equations. A subset of study participants and other key informants participated in interviews, and program staff in focus groups, to explore experiences with and perspectives regarding financial incentives. Qualitative data will be rigorously coded and thematically analyzed.

**Conclusions:** Findings from this study will contribute high quality evidence to an underdeveloped literature base on the effectiveness and acceptability of financial incentives to improve service engagement and health-related outcomes among adults experiencing homelessness and mental illness.

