### Measures

#### Quantitative Measures

The primary outcome is service engagement, or program attendance, measured as a count of health-care contacts with CATCH service providers per month over the 6-month period (or until discharge from the program). CATCH service providers record program participant attendance in health care appointments and care planning meetings lasting at least 5 min in participant health records. Eligible health-care contacts include in-person and virtual appointments, as well as care planning conversations through email or text. This definition is consistent with the current program practices and ensures only eligible health-care contacts are recorded and reported to the funding agency. Data on program attendance will be captured at study end through chart reviews by a blinded study staff.

Demographic data and other participant characteristics including residential status and income sources were collected by self-report at baseline. Secondary outcome measures of mental and physical health status, health service use, quality of life, and housing are being collected at baseline and 6 months and a measure of perceived therapeutic working alliance is collected at 6 months. Health service use will also be evaluated using data linkage of administrative health records, conducted at ICES, which holds population-based health and health service use information at the patient level for all Ontarians with health insurance.

See Table 1 for a detailed description of all quantitative measures.

**Table 1 T1:** Description of measures.

**Domain**	**Instrument**	**Description of instrument**

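### The primary outcome is defined in two ways, and the planned rate per programme-month gives no credit for any effect of the incentive on retention

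*Protocol article*

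**What the plan says.** The Abstract gives service engagement as the primary outcome, "measured by the count of participant-provider health-care contacts over the 6-month period post-randomization". Study Design agrees: it describes the number of contacts over a 6-month follow-up.

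Quantitative Measures has the outcome "measured as a count of health-care contacts with CATCH service providers per month over the 6-month period (or until discharge from the program"), and the service engagement row of Table 1 follows it. Primary Outcome Analysis explains that "program duration is customized for each participant, and may last between 1 and 6 months". For each participant it counts the months up to discharge and the contacts made in them. Total contacts are then modelled by Poisson regression with group as the only covariate and "an offset equal to the log (number of months spent on the program) will estimate the rate ratio and 95% confidence intervals".

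Three further statements bear on the point:
- Timing: "Participants were randomized following the baseline interview using block randomization", so most programme time comes after allocation.
- Payment: Study Design offers $20 for each week of meaningful engagement, for 6 months or until successful transition to longer-term supports.
- Principle: Secondary Outcome Analysis says that "all analyses will use the intention-to-treat principle".

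**The concern.** A count over a fixed 6 months and a rate per month until discharge are different estimands. They can differ in size and, in some circumstances, in direction. The analysis section fixes the model and offset explicitly, so this is not detail left for a fuller plan.

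The denominator is a post-randomisation quantity that the incentive may change. The Introduction names high drop-out as part of the problem to be solved. Yet if the clock stops when a participant leaves, someone with 5 contacts in 1 month and someone with 30 contacts in 6 months both score 5 per month. An incentive that works by keeping people in the programme could then be reported as having no effect. Primary Outcome Analysis does not separate disengagement from planned transition, and the article describes no comparison of time in programme by arm.

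**Working it through.** **The plan's own figure.** Inputs from Sample Size: 4.6 contacts per month under usual care, rate ratio 1.25, two-sided 5% level, 80% power, 22% attrition. The Signorini formula with 1:1 allocation, 1 month of exposure and no overdispersion is

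N = [1.96 × √4 + 0.8416 × √(2 + 2/1.25)]² / [4.6 × (ln 1.25)²] = 132.9,

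that is 66.4 per group, rounded up to 67. Attrition: 67/0.78 = 85.9, so 86 per group and 172 in total. The stated sample size reproduces, and it was set for a monthly rate.

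**What the model estimates.** With group as the only covariate, each arm's fitted rate is total contacts divided by total programme-months. Write C for mean contacts and M for mean months per participant (1 = incentive, 0 = usual care):
- planned ratio = (C1/M1)/(C0/M0)
- 6-month count ratio = C1/C0, with no contacts after leaving
- hence planned ratio = count ratio ÷ (M1/M0).

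Any difference in stay is divided out. This is algebra and needs no assumed figures. The document gives no mean stay, drop-out by arm or monthly profile, so every number below rests on assumed values for these.

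**(a) Equal intensity, different retention.** Both arms 4.6 per month; 30% versus 10% leave at 2 months and the rest stay 6.
- M0 = 0.3 × 2 + 0.7 × 6 = 4.8; M1 = 0.1 × 2 + 0.9 × 6 = 5.6.
- C0 = 4.6 × 4.8 = 22.08; C1 = 4.6 × 5.6 = 25.76.
- Planned ratio 4.6/4.6 = 1.00; count ratio 25.76/22.08 = 1.17.
- If the early leavers are drop-outs and their exposure is kept at 6 months, the monthly rates are 22.08/6 = 3.68 and 25.76/6 = 4.29, ratio 1.17.

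**(b) Tapering contacts, no rise in intensity.** Contacts of 7, 6, 5, 4, 3, 2 in successive months, both arms.
- Stay 4 versus 5 months: rates 22/4 = 5.5 and 25/5 = 5.0; planned ratio 0.91, count ratio 25/22 = 1.14.
- Stay 3 versus 5 months: rates 18/3 = 6.0 and 25/5 = 5.0; planned ratio 0.83, count ratio 25/18 = 1.39.

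**(c) Same taper, a true 25% rise in every month of the incentive arm.** Incentive rate 1.25 × 5.0 = 6.25.
- Stay 4 versus 5 months: planned ratio 6.25/5.5 = 1.14.
- Stay 3 versus 5 months: planned ratio 6.25/6.0 = 1.04, count ratio 31.25/18 = 1.74.
- The rise below which the planned ratio drops under 1 is 5.5/5.0, or 10%, in the first case and 6.0/5.0, or 20%, in the second. Both lie below the hypothesised 25%.

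**(d) The opposite direction.** Incentive arm 5.75 per month for 3.5 months, usual care 4.6 per month for 5 months: planned ratio 1.25, count ratio 20.125/23 = 0.875.

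**The case against.** Much can be said for the rate. Contacts per month while enrolled is a legitimate measure of intensity. It is the quantity in Sample Size, Quantitative Measures, Table 1 and the analysis section. Discharge may be a successful transition, which is an intended end of the programme, and the payment rewards attended meetings as well as staying. The fixed-window count has the mirror-image weakness: in (d) it falls below 1 although intensity rises by 25%, because earlier transition lowers it. Recruitment is complete and participants and study staff are unblinded, so replacing the primary estimand outright would be a substantive change, and power would have to be rechecked. All of this stands, and it argues for reporting the two measures together.

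It is also fair that the document does not say when a participant who disengages is discharged. If non-attenders stay enrolled, their months remain in the denominator and drop-out does lower the rate. Program Description gives a 3–6 month programme while the analysis allows stays from 1 month. That hints that early exits stop the clock but does not settle it.

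Two stronger readings are tempting. A reader might infer that the analysis breaks intention to treat; it excludes and reassigns nobody. A reader might also infer that longer retention will push the planned ratio below 1. That needs added months with fewer contacts than the comparison arm's mean rate and too small a rise in intensity to offset them.

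The objection does not remove the two definitions, or the fact that the denominator can respond to treatment.

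**Conclusion.** The point holds in this form. The article defines the primary outcome in two ways, and the planned model gives no credit for retention: at equal monthly rates its ratio is 1.00 whatever the difference in stay, against a count ratio of 1.17 in illustration (a). Participants are analysed as randomised, but the comparison is conditioned on a variable that treatment can affect.

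Reversal below 1 (0.91 and 0.83 in the examples) is conditional on tapering contacts and little or no rise in intensity. With a true 25% rise the ratio is attenuated to 1.14 or 1.04 and not reversed. The non-crediting is certain from the algebra if the clock stops at leaving. Its size in this trial is unknown, because stays, drop-out and taper are assumed. The document does not support a claim that the monthly rate is invalid or must be replaced.

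**What to change.** - Reconcile the Abstract, Study Design, Quantitative Measures, Table 1 and Primary Outcome Analysis into one stated primary estimand.
- State that disengagement or drop-out does not shorten exposure in the monthly rate; only planned transition, death or withdrawal of chart access can end it.
- Before outcome data are analysed, prespecify total eligible contacts from randomisation to 6 months for every randomised participant, without a programme-time offset, as a co-reported companion to the monthly rate.
- Report months in programme and reason for leaving by arm, and draw conclusions on engagement over 6 months only from the two measures together.

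The cost is wording in the plan and registry and one further analysis from the chart review already planned. The downside is that early successful transition lowers the fixed-window count, so it must be read alongside the reasons for leaving.
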